## 5.2 Method for Assigning Subjects to Treatment Groups

**Randomization:** Subjects will not be randomized until all entry (inclusion and exclusion) criteria have been met and all pre-study procedures have been satisfactorily completed. The study biostatistician will generate a randomization schedule using a random number program (e.g., SAS software via PROC PLAN). Subjects will be randomly assigned in a 1:1 ratio to receive one of the two treatment regimens (either 3 daily sequential bilateral aTBS sessions in the active arm or 3 daily sham sessions) for 10 days.

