### 4.1 Inclusion Criteria

Patients are eligible for participation if they are:

- Inpatients or outpatients
- Voluntary clinical patient with the capacity to assent (or consent if 18) to treatment and a parent or legal guardian with the capacity to consent (if younger than 18)
- Biological female or male (nonbinary or other gender identities are not exclusionary)
- 12-18 years of age
- Diagnosed with MDD based on Diagnostic and Statistical Manual for Mental Disorders, 5th edition (DSM-5) criteria with the Mini-International Neuropsychiatric Interview for Children and Adolescents (MINI Kid) in subjects 12-17 years of age; The Mini-International Neuropsychiatric Interview will be used for subjects who are 18 years of age
- In a current episode of MDD with duration of at least 4 weeks but less than 3 years
- Depressive symptom severity as demonstrated by CDRS-R total composite score of Forty or greater and a suicidal ideation score of 3 or more on item 13 of the CDRS-R
- A minimum score of 1 (“wish to be dead”) on the C-SSRS severity of ideation subscale
- Demonstrating that depressive symptom severity as evaluated at the screening visit does not improve between screening and baseline by 25% or more
- Eligible for transcranial magnetic stimulation (TMS) based on safety criteria
- On a medically acceptable form of birth control during the 10 day acute treatment course if female and of child bearing potential
- Taking an antidepressant medication if recommended by the referring clinician and agreed upon by parents and patients. Please note that patients are not required to take an antidepressant medication for study participation for practical, ethical, and human subject protection concerns. Medication status and prior treatment resistance will be carefully recorded with the Antidepressant Treatment History Form criteria for relevant statistical considerations.

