| CDRS-R – Childhood Depression Rating Scale – Revised                                                                                           | This is a validated, 17-item, clinician-rated tool to assess severity of depression. Parents provide input into 14 of the items. Total possible scores range from 17 to 113. Collected at screening, baseline, and weekly (after 5 treatments and posttreatment) during 10-day treatment and then monthly for 1 year follow-up period.            |
| CGI-S– Clinical Global Impressions Severity Scale                                                                                              | A standard measure of symptom severity and treatment response. Collected at screening, baseline, weekly (after 5 treatments and posttreatment) during 10-day treatment and then monthly for 1 year follow-up period.                                                                                                                              |
| C-SSRS – Columbia Suicide Severity Rating Scale                                                                                                | This is a validated, clinician-rated tool collected to assess lifetime and ongoing suicidal ideation and behavior at screening, baseline, daily during the 10 day treatment, then monthly for 1 year follow-up period. The severity of ideation subscale is a 5-point ordinal scale that is the primary clinical outcome measure for this study.  |
| Demographics Questionnaire                                                                                                                     | This is a self-reported questionnaire that collects the subjects gender, race, ethnicity, sexual orientation and educational levels of parents.                                                                                                                                                                                                                 |

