## 7 Statistical Plan

### 7.1 Sample Size Determination

#### Sample Size Estimation and Power Analysis for the Primary Aim of the Study

We established the sample size for the Primary Aim/Outcome/Hypothesis 1a (suicidal ideation over 10 days of acute sequential bilateral aTBS treatment) by incorporating a repeated measures design, with assumptions about potential participants (e.g., effect size/odds ratio), based on general guidance from a recent study that evaluated the effect of bilateral rTMS vs. sham stimulation on suicidal ideation in adult patients with treatment-resistant MDD. The results of the *a priori* sample size estimation and power analysis suggest that a sample size of 35 participants per group (N=70) achieves 80% power, at a 0.05 alpha level (two-tailed), to detect an overall odds ratio of 2.85 (sequential bilateral aTBS vs. Sham stimulation on lower-ordered intensity of suicidal ideation CSSR-S subscale scores—less suicidal ideation) in a 2 (between-subjects) group randomized design with 10 (within-subjects) repeated measurements of the primary ordinal outcome (suicidal ideation), when the proportion (or incident rate) of suicidal ideation from the sham group at the end of the 10-

day trial  $\geq 0.50$ , and the assumed within-subject correlation between observations (suicide ideation) on the same subject is  $\leq 0.50$  (0.50 was based on guidance from our preliminary TMS work). We note that the posited odds ratio of 2.85 for the current application is a bit more conservative than what was reported in the Weissman, et al. (2018) study of bilateral TMS vs. Sham stimulation on suicidal ideation in adult patients with treatment-resistant MDD (odds ratio=3.03).

We anticipate some dropouts (~10% based on treatment discontinuation results from our previous rTMS studies). Thus, ~80 participants will be enrolled to allow for this expected rate of attrition with the intent of capturing a range of evaluable data for 70 participants. The Power Analysis and Sample Size (PASS) 2019 software, version 14.0.15, was used to carry out the sample size and power analysis (PASS 2016, NCSS, Inc., Kaysville, Utah).

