### Primary Aim

#### Data Analysis Plan for Primary Aim 1 (Hypotheses 1a–1c)

##### Primary Outcome for Aim 1: Suicidal Ideation during the 10-day acute Trial Period

**Hypothesis 1a:** We expect 10 days of sequential bilateral aTBS will have greater efficacy for improving suicidal ideation in adolescents with MDD (as assessed by the C-SSRS severity of ideation subscale) over the 10-day acute treatment trial compared to sham stimulation.

Suicidal Ideation (as measured by the C-SSRS severity of ideation subscale) over the 10-day acute sequential bilateral aTBS trial period will be the primary ordinal outcome measure. The acute change over time (10 days) in Suicidal Ideation will be compared between the two treatment groups (sequential bilateral aTBS vs. sham stimulation) using an ordinal logistic regression model within a Generalized Estimating Equation (GEE) framework. The logistic model will contain fixed effects terms for treatment, time, treatment  $\times$  time interaction along with baseline C-SSRS severity of ideation subscale as a covariate. Age, sex, pubertal status, antidepressant medication status, and depression severity (CDRS-R total as a time-varying covariate) will also be included as covariates in the model. Simple treatment group effects in each time period will also be assessed. [see sensitivity analysis section below for missing not at random (MNAR) mechanism].

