##### Secondary Count Outcome for Aim 1: Emergency Department visits and Hospitalization visits during the 12 month Follow-up

**Hypothesis 1c:** We expect that adolescents who receive 10 days of sequential bilateral aTBS will have fewer emergency department visits and fewer hospitalization visits related to suicidality during the 12-months after the intervention compared to sham stimulation.

Emergency department visits and hospitalization visits related to suicidality will be assessed at monthly follow up visits over a 12-month period after the intervention. A separate Poisson

(or negative binomial) mixed model analysis will be used to estimate the number of emergency department visits and hospitalization visits, respectively, over the 12 months after intervention for those who received sequential bilateral aTBS vs. those who received sham stimulation. The model will contain fixed effects terms for treatment, time, treatment  $\times$  time interaction, and the same covariates identified in hypotheses 1a and 1b above. Simple treatment group effects in each time period will also be assessed. Maximum likelihood estimation, Type 3 tests of fixed effects, and generalized least squares means will be used along with the best fitting covariance structure. The sandwich (robust covariance matrix) estimator will also be considered. The Poisson model will be checked for overdispersion. The Poisson (or negative binomial) regression will model the logarithm of each outcome as a random variable, and the mean and variance will be estimated on the logarithmic scale. Thus, to facilitate interpretation, geometric means will be reported, which will be obtained by exponentiating the log-scaled parameter estimates. The procedures of PROC GLIMMIX in SAS software will be used to conduct the Poisson (or negative binomial) regression for Hypothesis 1c and provide a robust mechanism for handling data that are assumed missing at random (see sensitivity analysis section below for MNAR).

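### The covariate list fixed for H1b and H1c leaves out lifetime suicidal behaviour, which the screening C-SSRS records, and section 5.2 names no stratification factor for a mixed inpatient and outpatient sample

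*Protocol*

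**What the plan says.** - **Who enters.** Section 4.1 admits "Inpatients or outpatients". Section 4.3 recruits through outpatient clinics, the emergency department and an inpatient psychiatry unit. Section 1.5.2 (Suicidal Behavior) makes patients with past attempts eligible.
- **How they are allocated.** Section 5.2 has the biostatistician generate a schedule with a random number program: "Subjects will be randomly assigned in a 1:1 ratio to receive one of the two treatment regimens". It mentions neither strata nor blocks.
- **H1a model (section 7.2).** Treatment, time, their interaction and baseline C-SSRS ideation severity, and then: "Age, sex, pubertal status, antidepressant medication status, and depression severity (CDRS-R total as a time-varying covariate) will also be included as covariates in the model".
- **H1b model.** A similar model, with pharmacotherapy or psychotherapy received in follow-up to be considered as further covariates.
- **H1c model.** Poisson or negative binomial mixed models for the two event counts, with treatment, time, their interaction "and the same covariates identified in hypotheses 1a and 1b above".
- **What is recorded.** Table 4 (section 6.4) describes the C-SSRS as "collected to assess lifetime and ongoing suicidal ideation and behavior at screening" and at later visits. No row of the schedule of events (Table 3) names care setting at entry. Hospitalizations related to suicidality are scheduled for the monthly follow-up visits only.

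**The concern.** H1c counts emergency visits and admissions related to suicidality. Of the baseline information the trial collects, a history of suicidal behaviour is among the items closest to that outcome. Section 1.1 itself says that early ideation and attempts predict similar behaviour later in life. The ideation term already in the model measures thoughts and does not measure past behaviour. The covariate list is written into the protocol, so this is a choice made here and not something left to a later document.

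Care setting raises a related question. An adolescent in hospital at entry may well have a different 12-month risk of readmission from one in the community. With 35 to 40 per arm, a sizeable chance gap between arms is not unusual.

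At stake is how well the 12-month comparison is estimated. H1b and H1c are labelled secondary in section 7.2, but they sit under Primary Aim 1, and section 3.4 lists the same events as a primary safety endpoint. Section 2.1 says the pilot is meant to support pivotal studies, so the 12-month estimates will probably feed their planning.

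**Working it through.** **1. The plan's own figure.** Section 7.1 states that "a sample size of 35 participants per group (N=70) achieves 80% power". The inputs are a two-sided 5% level, a target odds ratio of 2.85, a sham proportion of 0.50, within-subject correlation 0.50 and 10 measurements.
- Second-arm proportion: 2.85 / (1 + 2.85) = 0.740.
- Repeated-measures factor: (1 + 9 × 0.5) / 10 = 0.55.
- Two proportions, pooled variance: 62.9 per arm at a single time; 62.9 × 0.55 = 34.6, so 35 per arm (power 80.5%). A Wald calculation on the log odds gives 36.2 (power 78.7% at 35).
- Dropout: 70 / 0.9 = 77.8, so 78, consistent with about 80 enrolled.

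The primary sample size reproduces and is not in dispute. The protocol gives no power, event rate, inpatient share or share with past attempts for the 12-month outcomes. Everything below therefore rests on assumed values.

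**2. Chance imbalance under simple 1:1 allocation.** For a binary factor with prevalence p and 40 per arm, the between-arm difference in share has SD √(2p(1−p)/40). At p = 0.35 this is √(0.455/40) = 0.107, so 95% of trials fall within about ±21 points. Exact (hypergeometric) probabilities for 80 subjects, 40 per arm:

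| Prevalence | Gap ≥ 15 points | Gap ≥ 20 points |
|---|---|---|
| 30% | 22.2% | 8.7% |
| 40% | 25.4% | 11.0% |
| 50% | 26.3% | 11.7% |

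**3. What a 20-point gap does to the crude rate ratio.** With 40% prevalence overall (50% in one arm, 30% in the other) and predictor rate ratio R, the shift is (1 + 0.5(R−1)) / (1 + 0.3(R−1)):
- R = 2: 1.5 / 1.3 = 1.15
- R = 3: 2.0 / 1.6 = 1.25
- R = 4: 2.5 / 1.9 = 1.32

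**4. What adjustment buys on H1c.** Simulated overdispersed yearly counts, 35 per arm, 1,500 trials per row. Assumptions: sham mean 1 event per year, gamma heterogeneity with variance 0.5, predictor prevalence 40%, robust Poisson regression. Power and SD are at a true treatment rate ratio of 0.5; type I error is at a ratio of 1.

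| R | Power without → with | SD of log rate ratio | Type I error without / with |
|---|---|---|---|
| 2 | 51.8% → 54.3% | 0.368 → 0.361 | 6.2% / 6.7% |
| 3 | 48.2% → 53.5% | 0.386 → 0.371 | 6.1% / 6.3% |
| 4 | 46.7% → 55.1% | 0.401 → 0.372 | 6.3% / 6.4% |

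The gains are 2.5, 5.3 and 8.4 points. Monte Carlo error on each power is √(0.25/1500) = 1.3 points, so the first gain is small beside the noise.

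**5. Closer to the planned model, and with weaker predictors.** A further simulation at 35 per arm kept baseline ideation and four other covariates in the model. It gave a 2 to 6% smaller spread of the log rate ratio and about 2 to 7 power points if the two predictors have rate ratios 3 and 2. If both have ratio 1.5, there was essentially no gain.

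**6. Stratifying without adjusting.** In the step 4 setting, with the factor balanced by design but left out of the model, the null rejection rate was 5.1%, 4.1% and 3.8% for R = 2, 3 and 4. With the factor in the model it was 6.4%, 5.9% and 6.4%, and power rose from 52.5% to 56.2%, 49.1% to 55.3% and 44.5% to 52.5%. A factor used to stratify should therefore also enter the model.

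No corresponding figure was worked out for H1b.

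**The case against.** The strongest reply is that the planned model is already reasonable. Baseline C-SSRS ideation severity, a direct measure of suicidality, is in it and may absorb part of what history would add. Chance imbalance under randomisation is already reflected in the standard error. The outcomes are secondary in a pilot whose size section 7.1 calls partly resource-driven. All of this stands, and it limits the point to a modest gain in precision.

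Several stronger readings are tempting, and the documents do not support them:

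- **That allocation is unstratified by decision.** Section 5.2 is silent. Strata or blocks may be set out in a randomisation plan or SAP that is not shown. What can be said is that the protocol names none.
- **That these are strong predictors.** No section gives a figure. Section 1.1 says early attempts predict later behaviour, but also that known risk factors have limited predictive value. *Plausible prognostic factor* is as far as the text goes.
- **That both factors are already on the case report form.** This is explicit only for lifetime behaviour. Setting must be known at eligibility review, but Table 3 has no row for it.
- **That H1c concerns rare events.** Section 8.5 expects attempts and psychiatric hospitalizations in follow-up to be common.
- **That a promise about treatment resistance is broken.** Sections 4.1 and 5.5 say that medication status and treatment resistance are recorded for statistical use. Medication status is in the models, and the sentence does not commit to treatment resistance as a covariate.
- **That pubertal status could be dropped to make room.** Section 1.1 says GABAergic function changes considerably during neurodevelopment, which is a reason to keep it.

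**Conclusion.** The point holds as a modest improvement to the 12-month analyses. The list fixed for H1b and H1c omits a baseline factor that is recorded, plausibly prognostic and closely tied to the H1c events. The protocol also names no balancing factor for a sample drawn from two care settings.

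The size is roughly 2 to 8 power points on H1c if the predictor's rate ratio is 2 to 4, and about nil at 1.5. This assumes 35 per arm, a treatment rate ratio of 0.5, a sham mean near one event per year and 40% prevalence, none of which the protocol supplies. In those simulations power stays below 60% with or without the change.

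A reader might infer that the 12-month comparison is biased or its test invalid. It is not: simulated type I error is about 6% with and without the covariate. The primary outcome's sample size is unaffected.

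**What to change.** 1. In section 7.2, add lifetime suicidal behaviour (yes/no, from the screening C-SSRS) to the prespecified baseline covariates for H1b and H1c.
2. Add care setting at entry (inpatient or outpatient) to the schedule of events and the case report form.
3. In section 5.2, name care setting as a stratification factor and carry it into the models, or leave allocation as described and enter setting as a baseline covariate. If a separate randomisation plan already stratifies, say so in section 5.2.
4. Keep pubertal status and the baseline ideation term.

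The cost is one added data field, possibly one stratum in the schedule, and one or two more parameters in a model with about 70 subjects. The change should be fixed before any unblinded 12-month data are seen.

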## 5.3 Preparation and Administration of Investigational Device

Preparation and administration of the TMS treatments will be consistent with procedures outlined by the MagVenture user manual and user training documentation.

## 5.4 Subject Compliance Monitoring

Non-adherence to the assigned treatment regimen is defined as missing  $\geq 2$  treatments days, or missing more than 20% of the total number of treatment sessions (i.e. 6 sessions) occurring during the 2 weeks of treatment as outlined in the schedule of events.

## 5.5 Prior and Concomitant Therapy

Reasonable efforts will be made to determine all somatic therapies for depression received by the participant in the past 2 years. All other medications and therapies received within six months of study enrollment will also be determined. All relevant information will be recorded on the Participants CRF. The ATHF will be completed to quantify treatment history.

During the trial, subjects will continue to take antidepressant medication if recommended by the referring clinician. Please note that subjects are not required to take an antidepressant medication for study participation for practical, ethical, and human subject protection concerns. Medication status and prior treatment resistance will be carefully recorded with the ATHF for relevant statistical considerations. The research team will collect information on subsequent pharmacological treatments during the 1-year follow up period.

Zaleplon, zolpidem, or zopiclone (1 dose nightly) as needed for treatment emergent insomnia or lorazepam (up to 2 mg daily) for treatment emergent anxiety, may be administered for up to 10 doses during the treatment phase of the study. The use of alternative hypnotics or anxiolytic compounds requires prior approval from the PI ([name]). Hormonal contraceptives are allowed. Short-term treatments for headaches, allergies, colds, and flu symptoms will be allowed during. All questions regarding the acceptability of specific medications must be approved by the PI/Sponsor ([name]).

## **5.6 Packaging and Labeling**

The MagVenture device will be clearly labeled with the following warning:

“CAUTION – Investigational Device. Limited by Federal (or United States) law to investigational use”

## **5.7 Masking/Blinding of Study**

**Blinding:** The use of the MagVenture Cool-B70 A/P coils facilitates blinding of the operator and subjects receiving aTBS or sham treatments. The study team members completing clinical rating scales will also not be allowed in the treatment suite during TBS treatment sessions and will be blinded to treatment assignment. A pre-post treatment expectancy and experience form will ask subjects and parents to make a guess regarding treatment arm (active or sham). Blinded study team members will also be asked to guess treatment assignments for each subject.

## **5.8 Receiving, Storage, Distribution and Return**

### **5.8.1 Receipt of Investigational Devices**

The MagVenture device will be delivered to the Principal Investigator/Sponsor and installed by MagVenture.

Upon receipt of the MagVenture TMS Therapy System and study treatment supplies, an inventory will be performed and a device accountability log completed by designated study staff. The designated study staff will count and verify that the shipment contains all the items noted in the shipping invoice. Any discrepancies or damaged or unusable devices in a given shipment will be documented in the device accountability log. The PI will notify MagVenture immediately of any discrepancies or damaged or unusable products.

### **5.8.2 Storage**

The supplies and disposables required for each treatment will be stored in a supply station separate from clinical practice stock.

### 5.8.3 Distribution of Study Device

The study team will maintain a local device accountability log noting treatments received by each participant with the device. Reconciliation and audits will take place at least annually.

### 5.8.4 Return or Destruction of Study Device

The MagVenture Devices that are loaned to the study site for purposes of this study will be returned to MagVenture at conclusion of the study. Remaining disposables and related study equipments that are remaining in the site study research inventory at the completion of the study will be packaged and returned to MagVenture.

## 6 Study Procedures

**Experimental Design:** This is a randomized, double-blind, sham-controlled trial of sequential bilateral aTBS in adolescents with depression and suicidal ideation (Figure 7). Three sessions are administered daily for 10 days (5 days per week). During each session, cTBS in which 1800 pulses are delivered continuously over 120 seconds to the right dorsolateral prefrontal cortex (RDPFC) is administered first, followed by iTBS in which 1800 pulses are delivered in 2 second bursts, repeated every 10 seconds for 570 seconds (1800 pulses) to the left dorsolateral prefrontal cortex (LDPFC). The TBS parameters were adopted from prior work, with 3-pulse 50 Hz bursts given every 200 ms (at 5 Hz) with an intensity of 80% of active MT. The comparison group will receive 3 daily session of bilateral sham TBS treatment for 10 days.

All subjects will receive standard of care treatment for depression and suicidal ideation including daily psychotherapeutic skill sessions (Figure 8). The 10-day psychotherapy treatment program was adapted from recent work and input from a consultant ([name]). The primary outcome measure is suicidal ideation assessed with the C-SSRS severity of ideation subscale. Depressive symptom severity will be assessed with the CDRS-R.

| Table 3. Schedule of Events                                                                                                   |                  |                 |                                              |                                                |                                 |                                                 |
|--------------------------------------------------------------------------------------------------------------------------------------|------------------|-----------------|----------------------------------------------|------------------------------------------------|---------------------------------|-------------------------------------------------|
| Study Activity                                                                                                                | Screening | Baseline | Daily aTBS and psychotherapy sessions | Posttreatment (End of 10-day treatment) | Monthly Follow-up Visits | Comments                                 |
| Consent and Assent                                                                                                                   | X                |                 |                                              |                                                |                                 |                                                 |
| Transcranial Magnetic Stimulation Safety Screen (TASS)                                                                               | X                |                 |                                              |                                                |                                 |                                                 |
| Antidepressant Treatment History Form (ATHF)                                                                                         | X                |                 |                                              |                                                |                                 |                                                 |
| Medical History                                                                                                                      | X                |                 |                                              |                                                |                                 |                                                 |
| Demographics Questionnaire                                                                                                           | X                |                 |                                              |                                                |                                 |                                                 |
| Physical Exam                                                                                                                        | X                |                 |                                              |                                                |                                 |                                                 |
| Vital Signs                                                                                                                          | X                |                 |                                              | X                                              |                                 |                                                 |
| Pubertal Development Scale (self-assessment)                                                                                         | X                |                 |                                              |                                                |                                 |                                                 |
| Urine Drug Screen                                                                                                                    | X                |                 |                                              |                                                |                                 |                                                 |
| Urine Pregnancy Screen (if applicable)                                                                                               | X                |                 |                                              |                                                |                                 |                                                 |
| Auditory thresholds                                                                                                                  |                  | X               |                                              | X                                              |                                 |                                                 |
| Mini-International Neuropsychiatric Interview for Children and Adolescents (MINI Kid) Adult version used for subjects who are age 18 | X                |                 |                                              |                                                |                                 |                                                 |
| NIH Toolbox Cognition Battery                                                                                                        |                  | X               |                                              | X                                              |                                 |                                                 |
| The Brief Affective Personality Scale                                                                                                | X                |                 |                                              |                                                |                                 |                                                 |
| Young Mania Rating Scale (YMRS)                                                                                                      | X                | X               | X                                            | X                                              | X                               | Collected weekly during 10-day treatment period |
| Childhood Depression Rating Scale – Revised (CDRS-R)                                                                                 | X                | X               | X                                            | X                                              | X                               | Collected weekly during 10 day treatment period |
| Columbia Suicide Severity Rating Scale (C-SSRS)                                                                                      | X                | X               | X                                            | X                                              | X                               | Collected daily during 10 day treatment period  |
| Childhood Trauma Questionnaire                                                                                                       | X                |                 |                                              |                                                |                                 |                                                 |
| Beck Depression Inventory-II (BDI-II)                                                                                                | X                | X               |                                              | X                                              | X                               | Collected weekly during 10 day treatment period |

|                                                                                      |   |   |   |   |   |                                                 |
|--------------------------------------------------------------------------------------|---|---|---|---|---|-------------------------------------------------|
| Pre/Post Treatment Expectations and Experience Questionnaire (Adolescent and Parent) |   | X |   | X |   |                                                 |
| Clinical Global Impressions Severity Scale (CGI-S)                                   | X | X | X | X | X | Collected weekly during 10 day treatment period |
| Concurrent Medications                                                               | X | X | X | X | X |                                                 |
| Adverse Events                                                                       | X | X | X | X | X |                                                 |
| Serious Adverse Events                                                               | X | X | X | X | X |                                                 |
| TMS Neurophysiology Measures (TMS-EMG LICI-100 and TMS-EEG LICI-100 and N100)        |   | X |   | X |   |                                                 |
| Case Report Forms                                                                    | X | X | X | X | X |                                                 |
| Concurrent Psychotherapy                                                             | X | X | X | X | X |                                                 |
| Concurrent Medications                                                               | X | X | X | X | X |                                                 |
| Hospitalizations Related to Suicidality Noted                                        |   |   |   |   | X |                                                 |
| Emergency Department Visits Related to Suicidality Noted                             |   |   |   |   | X |                                                 |

## 6.1 Visit 1

Table 3 describes the schedule of events. Table 4 describes all study assessments. The first visit is a screening visit. Informed consent and assent will be completed. A medical history, physical exam, vital signs, urine pregnancy test (if applicable) and urine drug screen will be completed. The subject's parent or guardian will not be told the results of the pregnancy test without the subject's permission. But if the study physician believes that being pregnant may cause serious health problems, they may need to tell the parent or guardian the test results. Patients with a positive urine drug screen that are not due to prescribed drugs are not eligible for study participation. The study physician will ask if the results can be shared with the parent or guardian. This information will be kept confidential if the subject chooses not to share the drug test results with the parent or guardian. The results of the urine drug test will not become part of the medical record, but the results will remain in the study record. Additional screening assessments include: the Transcranial Magnetic Stimulation Safety Screen (TASS), Antidepressant Treatment History Form (ATHF), pubertal development scale (PDS), Mini-International Neuropsychiatric Interview (MINI Kid for ages 12-17 and MINI for age 18), Young Mania Rating Scale (YMRS), Children's Depression Rating Scale Revised (CDRS-R), Columbia Suicide Severity Rating Scale (C-SSRS), Beck Depression Interview-II (BDI-2), Clinical Global Impressions Severity Scale (CGI-S), concurrent medications, adverse events, serious adverse events, demographics questionnaire, case report forms, and concurrent psychotherapy. The screening visit can occur on the same day or across 2 consecutive days based on participant preference.

## 6.2 Visit 2

After eligibility is confirmed, additional assessments will be completed (Table 3 and 4). These assessments include auditory thresholds, NIH Toolbox Cognition Battery, YMRS, CDRS-R, C-SSRS, BDI-2, Pre/Post Treatment Expectations CGI, concurrent medications, adverse events, serious adverse events, case report forms, concurrent psychotherapy. TMS neurophysiology measures are collected. The participant is randomized to the active aTBS group or sham aTBS. Coil localization (Beam F3) and motor threshold procedures are completed. The participant will complete day one of aTBS treatment (either 3 active sequential bilateral TBS or 3 bilateral sham treatments).

